## Abstract

**Background:**

The use of structured curricula for minimally invasive surgery training is becoming increasingly popular. However, many laparoscopic training programs still use basic skills and isolated task training, despite increasing evidence to support the use of training models with higher functional resemblance, such as whole procedural modules. In contrast to basic skills training, procedural training involves several cognitive skills such as elements of planning, movement integration, and how to avoid adverse events. The objective of this trial is to investigate the specificity of procedural practice in laparoscopic simulator training.

**Methods/Design:**

A randomised single-centre educational superiority trial. Participants are 96 surgical novices (medical students) without prior laparoscopic experience. Participants start by practicing a series of basic skills tasks to a predefined proficiency level on a virtual reality laparoscopy simulator. Upon reaching proficiency, the participants are randomised to either the intervention group, which practices two procedures (an appendectomy followed by a salpingectomy) or to the control group, practicing only one procedure (a salpingectomy) on the simulator. 1:1 central randomisation is used and participants are stratified by sex and time to complete the basic skills. Data collection is done at a surgical skills centre.

The primary outcome is the number of repetitions required to reach a predefined proficiency level on the salpingectomy module. The secondary outcome is the total training time to proficiency. The improvement in motor skills and effect on cognitive load are also explored.

**Discussion:**

The results of this trial might provide new knowledge on how the technical part of surgical training curricula should be comprised in the future. To examine the specificity of practice in procedural simulator training is of great importance in order to develop more comprehensive surgical curricula.

**Trial registration:**

ClinicalTrials.gov: NCT02069951

## Background

Laparoscopic simulation training has become important in the acquisition of laparoscopic skills before operating on patients. Skills are ideally acquired through a structured curriculum using both feedback and predefined training goals [1]. Although there is a consensus that the curriculum should include a technical skills component, few studies have been conducted on exactly which technical skills should be included [2, 3]. Currently, there are only a few procedural modules for laparoscopy with solid evidence of the validity of metrics, including definition of proficiency levels [4]. In addition, many training curricula focus on isolated task training and do not incorporate procedural training [5]. Complex skills such as procedural training differ from isolated task training, as they involve more cognitive elements like planning, decision-making, and integration of isolated skills. When learning more complex skills in laparoscopic surgery, practicing only basic skills has not proven to be an effective strategy [6].

However, some of the elements practiced during procedural training may be transferable between different procedures. Thus, it is relevant to examine if repeated procedural simulator practice is relevant, which in turn will help develop the most sustainable curricula for minimally invasive surgical skills. Previous research have shown contradictory results; while some studies have found that laparoscopic skills are generalisable, other studies have found a high degree of task specificity for procedural training [7–9].

The objective of this trial is to examine the specificity of proficiency-based procedural simulator training and to examine transferability between two different procedural modules. Our hypothesis is that the same cognitive processes are utilised in the practicing of different complex laparoscopic tasks, like procedural training, and therefore these processes are transferable between different tasks.

## Methods and design

### Design

The trial is a randomised single-centre educational superiority trial.

### Participants

Participants are medical students recruited through an invitation distributed to student associations for general surgery and gynaecology and through a student newspaper. Inclusion criteria are: (1) enrolled at the Faculty of Health Science at the University of Copenhagen, (2) a bachelor’s degree in medicine, and (3) signed informed consent. Exclusion criteria are: (1) having previously participated in a trial involving laparoscopic training, (2) having performed laparoscopic surgery (>0 procedures), and (3) not speaking Danish at a conversational level. Every participant receives a unique trial identification number upon enrolment.

### Intervention

Participants are invited to participate in an introductory meeting in which information on the trial is given. All participants are informed verbally and in writing by the principal investigator before giving written informed consent. Participants can book three-hour training sessions through an online booking system; only one training session per day is permitted. Training sessions take place at the surgical skills centre at Rigshospitalet, University of Copenhagen. At the first training session, the participants are introduced to the simulator equipment by the principal investigator, and instructed on how to use it. The principal investigator supervises all training sessions and observes that the participants use both correct operating technique and handle instruments correctly. Participants start by practicing six basic skills tasks for isolated skills until they reach a predefined proficiency level for all tasks. The basic skills tasks do not have to be passed in any specific order. After each attempt, the simulator shows the participants automated feedback on each of the different measured parameters. Further more, the principal investigator provides feedback on request. The performance parameters and the predefined proficiency levels for each basic skill modules are listed in Table 1. Upon reaching proficiency for all tasks, the participants are randomised. Those randomised to the intervention group practice two procedures on the simulator to a predefined proficiency level: a laparoscopic appendectomy performed using endoloop technique (procedure A) and followed by a laparoscopic salpingectomy due to an ectopic pregnancy (procedure B). The control group only practices procedure B, Figure 1. The performance parameters and requirements for the predefined proficiency levels for procedures A and B are listed in Table 2. When practicing the two procedural modules, instructor feedback is provided after the first and tenth repetition [10]. The feedback is standardised and focuses on correct technique, instrument handling, and use of diathermy. For both the basic skills modules and the procedural modules, written instructions and video examples of the tasks are available for the participants and can be used at their own discretion. The predefined proficiency level for each module is reached when all of the requirements for the performance parameters is met simultaneously. This has to be archived for two attempts within five consecutive repetitions. The predefined proficiency levels are based on previous studies by the research group [1, 11]. Each participant is expected to use between six and twelve hours within a period of two months to complete the training program.

**Table 1 Tab1:** **Performance parameters and requirements for the basic skills modules**

	Requirements for proficiency level for basic skills modules (maximum values)					
Performance parameters	1: Coordination	2: Instrument navigation	3: Grasping	4: Lifting and grasping	5: Fine dissection	6: Cutting
Total time (s)	150	-	-	120	150	200
Right instrument path length (m)	3	1.4	2	3.2	-	1.8
Right instrument angular path (degrees)	750	250	300	600	-	400
Right instrument time (s)	-	25	45	-	-	-
Right instrument misses (#/%)	-	2	-	60	-	-
Right instrument outside of view	4	-	-	-	-	-
Grasper collided with right box (#)	-	-	-	10	-	-
Right box lifted (#)	-	-	-	15	-	-
Left instrument path lenght (m)	0.8	1.4	2	3.2	-	2
Left instrument angular path (degrees)	300	250	300	600	-	400
Left instrument time (s)	-	25	45	-	-	-
Left instrument misses (#)	-	2	-	60	-	-
Left instrument outside of view	-	-	-	-	-	-
Grasper collided with left box (#)	-	-	-	10	-	-
Left box lifted (#)	-	-	-	15	-	-
Tissue damage (#)	5	-	3	5	-	10
Maximum damage (mm)	10	10	5	15	-	25
Misses (%)	12	-	-	-	-	-
Ripped or burned blood vessels (%)	-	-	-	-	0	-
Energy damaged on blood vessels (%)	-	-	-	-	20	-
Ripped small vessels (%)	-	-	-	-	25	-
Burned small blood vessels w/o stretch (%)	-	-	-	-	25	-
Rip failure (%)	-	-	-	-	-	25
Drop failure (%)	-	-	-	-	-	25
Max stretch damage	-	-	-	-	-	100

- : Not measure for the specific exercise.

**Figure 1 Fig1:**
[figure not shown]
**Participant flowchart in accordance with the CONSORT statement.**

**Table 2 Tab2:** **Performance parameters and requirements for procedural modules A and B- : not measured for the specific module**

	Requirements for proficiency level for procedural modules (maximum values)	
Performance parameters	Procedure A: Appendectomy	Procedure B: Salpingectomy
Total time (s)	290	280
Right instrument path length (m)	5	3
Right instrument angular path (degrees)	710	450
Left instrument path length (m)	4	2
Left instrument angular path (degrees)	930	350
Pressure damage to appendix (#)	3	-
Appendix Grasping time (s)	3	-
Burn damage to cecum (#)	7	-
Distal loop correctly applied (Y/N)	Y	-
Proximal loops correctly applied (Y/N)	Y	-
Appendix divided	Y	-
Blood loss (ml)	-	180
Pool of blood (ml)	-	10
Ovary Diathermy damage (s)	-	3
Tube Cut: Uterus distance (mm)	-	3
Removed dissected tissue (Yes/No)	-	Y
Bleeding vessel cut (Yes/No)	-	Y

- : Not measured for the specific module.

### Simulation equipment

Four simulator stations, each with the virtual reality simulator LapSim® (Software Version 2013) from Surgical Science (Gothenburg, Sweden), are used. The station’s height is adjustable and consists of a 27” monitor, which is attached to a gaming computer with a pair of Simball 4D Joystick from G-coder Systems (Gothenburg, Sweden). All computers are connected to a local server containing an electronic database storing the data generated after each attempt on the simulator. Training stations are separated using wall dividers and there is a pair of noise cancelling Bose Quiet Comfort III earphones at each station. This reduces possible distractions and prevents participants from observing and interacting with each other during practice sessions.

### Randomisation

Copenhagen Trial Unit is responsible for a central computerised 1:1 randomisation. The allocation sequence is computer-generated, with a varying block size kept concealed from the investigator. A web-based response system is used to allocate participants after they have completed the basic skills modules (see Intervention). The stratification variables are sex (male/female) and training time to reach proficiency for all basic tasks (less than or equal to two hours/more than two hours).

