### Sample size determination

Based on a previous study we expect the control group to take approximately 30 repetitions to reach the proficiency level, with a standard deviation of 15 [10]. A minimal difference of 10 repetitions between the two groups is deemed clinically relevant, meaning that the intervention group is expected to take approximately 20 repetitions to reach proficiency. The standard deviation is assumed to be equal in both groups. With alpha set to 0.05 and beta to 0.10 we need 48 participants in each group, totalling 96 participants.

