### Statistical analysis

Data will be analysed using SPSS (Chicago IL, version 20.0), SAS statistical software (SAS Institute Inc., Cary NC, version 9.4) and the statistical software package R (version 3.0.3). A two-sided significance level of 0.05 will be used. The primary and secondary outcomes will be compared using the normal linear multivariable model, adjusting for the two stratification variables. If the assumptions of normality and homogeneity of variance are not sufficiently fulfilled, the outcome data will be transformed. If the assumptions cannot be met by transformation either robust regression, weighted least squares, or bootstrap methods will be applied. If none of these methods seem to give an adequate description of the data, the intervention and control group will be compared using the van Elteren test, and a non-parametric estimate of the confidence interval of the intervention effect will be obtained by bootstrapping [16, 17]. The p-values obtained for secondary and exploratory outcomes will be adjusted for multiplicity using the Benjamin-Hochberg procedure [18].

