### Trial strengths and limitations

The strength of the present trial is the use of a trial design that mirrors an actual curriculum, because it incorporates both proficiency-based training and distributed practice [29]. Therefore, the findings can probably be applied to actual training in simulation centres. The use of basic skills training to ensure the same proficiency level before randomisation helps standardise the intervention with the procedural modules because the participants have a similar starting point in terms of basic laparoscopic skills. Additionally, use of the same training equipment minimises the risk of confounding from variations in training conditions.

The trial is designed in order to minimise the risks of systematic errors and the risks of random errors [30–32]. Systematic errors have been sought to be reduced by central randomisation stratified for prognostic factors [30–32]. Blinding is used whenever possible and data is analysed according to the intention-to-treat principle. We are aware that some outcomes are at risk of being assessed with some bias, as they are not possible to blind [30–32].

A limitation is the trial participants are medical students instead of novice surgical residents; however, previous studies have shown that medical students’ performance on the simulator is similar to that of novice surgical residents [10, 11]. There are only approximately 50 first-year residents in surgery and gynaecology in the region every year, and they vary greatly in laparoscopic experience; thus, the trial would not have been feasible with first-year residents. Ideally, the trial should include transfer to the clinical settings using clinical outcomes, but this is not feasible due to the large sample size that is required and the difficulty with finding relevant clinical outcomes [33].

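### Basic-skills training time enters the primary and secondary models only as a two-hour split; adding the exact time as a continuous covariate would gain some precision at almost no cost

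*Protocol article*

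**What the plan says.** The Randomisation section of the protocol article names two stratification variables: sex, and "training time to reach proficiency for all basic tasks (less than or equal to two hours/more than two hours"). Participants are allocated only after they have finished the basic skills modules.

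The Statistical analysis section specifies a normal linear model for the primary outcome (repetitions to proficiency on procedure B) and the secondary outcome (effective training time on procedure B), "adjusting for the two stratification variables". No further covariate is listed. For the exploratory outcomes the section mentions only the multiplicity adjustment. The van Elteren test is the last fallback.

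The section on strengths and limitations describes the design as "central randomisation stratified for prognostic factors". The Simulation equipment section says that a server database keeps the simulator data from every attempt. No correlation between basic-skills time and either outcome, no distribution of that time and no reason for the two-hour cut is given.

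**The concern.** Time to proficiency on the basic tasks is a baseline measure of learning speed. It is taken on the same simulator as the outcomes and under the same kind of proficiency rule, and the secondary outcome is itself a training time. An association with the outcomes is plausible, and the article itself calls the stratification factors prognostic.

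Reducing such a measure to two levels treats everyone on the same side of two hours as alike. Whatever the exact time would explain within each side stays in the residual. If the association is real, the confidence interval for the treatment effect is wider than it need be with the same participants. Precision in the primary and secondary comparisons is all that is at stake.

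**Working it through.** **1. The plan's own sample size.** Inputs from Sample size determination and Statistical analysis: "we expect the control group to take approximately 30 repetitions to reach the proficiency level, with a standard deviation of 15"; "A minimal difference of 10 repetitions between the two groups is deemed clinically relevant"; "The standard deviation is assumed to be equal in both groups"; "A two-sided significance level of 0.05 will be used"; power 0.90.

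n per group = 2 × (1.960 + 1.282)² × 15² / 10² = 2 × 10.51 × 2.25 = 47.3, rounded up to 48, or 96 in total. This agrees with "With alpha set to 0.05 and beta to 0.10 we need 48 participants in each group, totalling 96 participants". Power at 48 per group is 90.4% by the normal approximation (89.8% with the t distribution). The calculation uses the full SD of 15, so it counts on no gain from covariates.

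**2. Is the exact time available?** The stratum depends on training time and must be known at allocation, and simulator data are kept for every attempt. The exact value should therefore exist before randomisation for all randomised participants. This is inferred; the article does not state it.

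**3. What a split retains.** For a normally distributed covariate, linearly related to the outcome and cut so that a share p lies on one side, the split keeps the fraction k = φ(c)² / [p(1 − p)] of the variance that the continuous covariate explains. Here c is the cut point and φ the normal density.

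- 50/50: 0.3989² / 0.25 = 0.637
- 80/20: 0.2800² / 0.16 = 0.490
- 90/10: 0.1755² / 0.09 = 0.342

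**4. Effect on the treatment comparison.** With correlation r between time and outcome, the residual variance as a share of the total is 1 − r² with continuous time and 1 − k·r² with the split. Their ratio is the ratio of the variances of the treatment effect. The 95% CI half-width is 1.96 × 15 × √(residual share × 2/48). Power is by the normal approximation at 48 per group.

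The values of r and p are assumptions. So are bivariate normality and linearity, possibly after transforming time. Variance shared with sex is ignored.

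| r | Cut | Residual share, split | Residual share, continuous | Variance ratio | Half-width, split / continuous (repetitions) | Power, split / continuous |
|---|---|---|---|---|---|---|
| 0 | any | 1.000 | 1.000 | 1.000 | 6.00 / 6.00 | 90.4% / 90.4% |
| 0.2 | 50/50 | 0.975 | 0.960 | 1.015 | 5.92 / 5.88 | 91.1% / 91.5% |
| 0.2 | 90/10 | 0.986 | 0.960 | 1.027 | 5.96 / 5.88 | 90.8% / 91.5% |
| 0.3 | 50/50 | 0.943 | 0.910 | 1.036 | 5.83 / 5.72 | 92.0% / 92.8% |
| 0.3 | 80/20 | 0.956 | 0.910 | 1.050 | 5.87 / 5.72 | 91.6% / 92.8% |
| 0.3 | 90/10 | 0.969 | 0.910 | 1.065 | 5.91 / 5.72 | 91.3% / 92.8% |
| 0.5 | 50/50 | 0.841 | 0.750 | 1.121 | 5.50 / 5.20 | 94.5% / 96.5% |
| 0.5 | 80/20 | 0.878 | 0.750 | 1.170 | 5.62 / 5.20 | 93.7% / 96.5% |
| 0.5 | 90/10 | 0.914 | 0.750 | 1.219 | 5.74 / 5.20 | 92.7% / 96.5% |

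In every row the split gives at least the 90.4% of step 1. The loss is measured against what continuous time could deliver, not against the plan.

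**The case against.** The strongest reply is that nothing here is in error. Adjusting for the factors as used in stratification is standard practice, matches the randomisation and needs no assumption about the shape of the relation with a time that is probably skewed. Stratified blocks need categories, so the cut in the Randomisation section is necessary. The van Elteren fallback needs the strata as well. All of this stands, and it is why the point concerns only the covariate list in the Statistical analysis section.

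It can also be said that a condensed article leaves covariate coding to the full analysis plan. That stands in part: if the full plan already enters time as a continuous covariate, the point falls away. But the article does state the covariate set, and defines one member of it as a two-level factor.

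The size of the loss rests wholly on assumed figures. Being called prognostic does not say how strongly a factor predicts. At r = 0.3 the power difference is only 0.8 points (median cut) to 1.5 points (90/10 cut).

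A reader might infer three stronger claims, none of which the document supports:

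- **The trial is short of power.** At r = 0.5 the variance ratios correspond to 96 × (1 − 1/1.121) ≈ 10 to 96 × (1 − 1/1.219) ≈ 17 participants. That is a forgone bonus on an assumed correlation, not a shortfall, because the sample size relies on no covariate.
- **The exploratory outcomes lose precision too.** The adjusted model is specified only for the primary and secondary outcomes.
- **Chance imbalance in time within strata is a defect.** It is ordinary random variation and is covered by the standard error.

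**Conclusion.** The point holds as a modest efficiency recommendation for the primary and secondary analyses. As written, the models use only the two-hour split of a baseline measure whose exact value should be on file. Relative to continuous time, the variance of the treatment effect is about 4% to 7% larger at an assumed correlation of 0.3, and about 12% to 22% larger at 0.5, from a median cut to a 90/10 cut. At r = 0.5 the confidence interval half-width would be 5.50 to 5.74 repetitions instead of 5.20, against a relevant difference of 10. With no correlation the loss is nil.

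The split introduces no bias, does not inflate type I error and does not impair the planned 90% power. The loss becomes material only if the correlation is strong or the cut very uneven, and the article does not allow either to be judged.

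**What to change.** In the Statistical analysis section, keep sex and the two-hour stratum as covariates and add basic-skills training time as a prespecified continuous covariate for the primary and secondary outcomes. The functional form should be fixed before the data are analysed; a log transformation is one reasonable choice for a skewed time, although nothing in the article dictates it. The two-hour cut stays as it is for the randomisation and for the van Elteren strata.

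The cost is one phrase and one residual degree of freedom: 96 − 4 = 92 with intercept, group, sex and stratum; 91 after the addition. It also brings an assumed shape for the relation with time. Under 1:1 randomisation a wrong shape mainly costs efficiency, and keeping the stratum in the model respects the design. According to Trial status, randomisation was still under way, so the change could be made before any analysis. It should first be confirmed that the exact time is retained for every participant.

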### Blinding

Because of the nature of the intervention, it is not possible to blind the participants and the principal investigator to the allocation of the participants. Data entry is performed independently, without the involvement of the principal investigator. All forms are entered in a database using double data entry by external personal. A person other than the principal investigator, who is familiar with the simulator equipment, performs external data monitoring of the simulator data during the trial. The statistical analysis is blinded and the statistician is not aware of the intervention allocation of participants during the analysis; this is done with the two groups, coded as X and Y. After the analysis, two conclusions are drawn by the steering committee with the blinding intact; one conclusion assuming X is in the intervention group and Y is in the control group, and one conclusion assuming the opposite. Only thereafter is the randomisation code broken.

